### Data management

Double data entry will be performed by two research staff independently. To ensure confidentiality, all documents obtained in this study will be kept strictly in a lockable filing cabinet in the office for at least 5 years after this study, before being destroyed using a shredder and discarded.

### Statistical design

The primary outcome will be analyzed with Fisher’s exact test according to the intention-to-treat principle. Participants who discontinue or deviate from the intervention protocols or with any missing data will be excluded. No additional analyses will be performed.

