### Sample size

No previous clinical studies have investigated the effectiveness of CAREDYNE Shield on DH; therefore, at least 15 participants will be required in each group to perform a sample size calculation in a subsequent study [15]. With a 20% dropout rate, a total of 40 participants will be recruited in this study.

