### Intervention

After randomized allocation, the participants in the intervention group will be treated with CAREDYNE Shield, and those in the control group will be treated with Nanoseal by the operator who performed allocation. Prior to the application of CAREDYNE Shield or Nanoseal, dental prophylaxis and water rinse will be performed to remove plaque deposits; the areas to be treated will be isolated with cotton rolls and dried with cotton pellets; two equal proportions of solution A and solution B will be mixed with a micro-brush and applied to the dentin surface for 20 s, followed by rinsing with water. Four weeks after the treatment, clinical assessments will be performed by the examiner who enrolled the participant in this study.

During this study, any other dental treatment to DH teeth are prohibited, and all intervention procedures will be recorded by the operator in an electronic chart to improve adherence to intervention protocols. Discontinuing intervention will be performed in the following case: (1) participant requests to stop or change the allocated intervention, (2) worsening disease or new disease occurs or (3) continuing this study is judged to be inappropriate.

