## Discussion

Several limitations associated with the present study warrant mention. First, blinding of operators will not be performed; therefore, the risk of bias in this domain may be unavoidable. Second, the data will be collected just after the participant’s training. Thus, VRS which is easier to understand for participants than a visual analog scale (VAS) will be performed; however, VRS is considered to be less sensitive than VAS [18, 19]. Third, it has been recommended that at least three different stimuli, specifically tactile, cold and air stimuli, should be used for clinical assessments of DH because DH may differ among stimuli [2]. However, only air stimuli will be evaluated in the present study because this study is being performed for sample size calculations, which is based on the primary outcome: the reduction of pain intensity in response to air stimuli. Tactile stimuli will be evaluated as a secondary outcome in a future, large-scale study. The GI and PI will be used as secondary outcomes in the present study. If a reduction in either is observed, the effectiveness of CAREDYNE Shield for the reduction of the GI and PI will be investigated in a future clinical study.

Desensitizers like CAREDYNE Shield and Nanoseal that induce chemical occlusion of dentinal tubules are biocompatible and react only with tooth substance; they can, therefore, be casually applied to subgingival areas and proximal surfaces. Furthermore, for several decades, in-vitro studies have investigated the function of zinc and reported that zinc reduced the demineralization of enamel and dentin and inhibited dentin collagen degradation, plaque growth and biofilm formation [20–24]. Thus, CAREDYNE Shield, which releases zinc ions, may be a useful novel desensitizer that acts not only as a desensitizer but also as a root caries inhibitor.

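### The primary analysis is labelled intention-to-treat, but the exclusions written next to it make it a per-protocol complete-case analysis

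*Protocol article*

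**What the plan says.** Three consecutive sentences in the protocol article, Methods/design, Statistical design, fix the primary analysis:

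- The first names the test and the principle: "The primary outcome will be analyzed with Fisher’s exact test according to the intention-to-treat principle".
- The second sets out who is left out: "Participants who discontinue or deviate from the intervention protocols or with any missing data will be excluded".
- The third closes off anything further: "No additional analyses will be performed".

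The Intervention section gives the reasons for discontinuing. The first is "participant requests to stop or change the allocated intervention"; the others are "worsening disease or new disease occurs or (3) continuing this study is judged to be inappropriate". The same section prohibits other dental treatment to the study teeth and has the operator record the intervention procedures.

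The Discussion states that "blinding of operators will not be performed; therefore, the risk of bias in this domain may be unavoidable". The Sample size section explains what the pilot is for: "at least 15 participants will be required in each group to perform a sample size calculation in a subsequent study", with a 20% dropout allowance and 40 participants in total.

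No section defines a second analysis set or limits the exclusions to a secondary analysis.

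**The concern.** Intention-to-treat keeps each randomised participant in the allocated arm whatever happens after allocation. The exclusion sentence removes three kinds of participant after allocation: those who discontinue, those who deviate, and those with any item missing. Leaving out only unobserved outcomes could be defended as an available-case analysis by allocated arm. Removing discontinuers and deviators whose 4-week pain score was recorded cannot be called ITT.

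Two features make this more than a labelling slip. First, some reasons for leaving the analysis set may be linked to outcome. A participant who asks to change treatment, or whose condition worsens, may be a poor responder. A participant with persisting pain who receives other treatment on the tooth may count as a deviator. Second, read literally, the missing-data clause could drop a participant with a complete verbal rating scale (VRS) score because a Gingival Index (GI) or Plaque Index (PI) is absent.

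At stake are the response rates that this pilot hands to the later sample size calculation, and a reader's trust in a label that does not describe the analysis.

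**Working it through.** **1. The plan's own figure.** Inputs from the Sample size section: 15 per group, 20% dropout, 40 in total.
- 15 / (1 − 0.20) = 18.75, so 19 per group and 38 in total. The stated 40 is within 2 participants and fits rounding up to 20 per group.
- 40 × 0.80 = 32, or 16 per group, which meets the minimum of 15.

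The sample size is not in dispute. The document gives no alpha, power or effect size, so there is no power figure to reproduce.

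**2. Who is analysed under each sentence.**

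| Participant | ITT sentence | Exclusion sentence |
|---|---|---|
| Discontinued, week-4 VRS observed | kept | removed |
| Deviated, week-4 VRS observed | kept | removed |
| VRS complete, GI or PI missing | kept | removed (literal reading) |
| Week-4 VRS missing | kept, needs a stated rule | removed |

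The sentences disagree in every row. The first two rows are the clearest breach.

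**3. What exclusions of this size could do.** Assumptions not in the document: a binary response, 4 of 20 excluded per arm (the 20% allowance, evenly split), and 14/16 v 8/16 responders among those kept.
- Kept set: 87.5% − 50.0% = 37.5 points, Fisher p = 0.054.
- All randomised: difference = (14 + x − 8 − y) / 20, where x and y are the responders among the 4 excluded in each arm, each from 0 to 4.
- Lowest (x = 0, y = 4): 14/20 v 12/20 = 10 points, p = 0.74.
- Highest (x = 4, y = 0): 18/20 v 8/20 = 50 points, p = 0.002.
- All 8 counted as not improved (x = y = 0): 14/20 v 8/20 = 30 points, p = 0.11.

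The range is 40 points wide, centred on 6/20 = 30 points and not on the 37.5 observed in the kept set.

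**4. How much of that belongs to the rule.** If all 8 simply missed week 4, their scores would be unobserved under ITT too, and the range is the price of missing data. If all 8 had a recorded score and were removed for discontinuing or deviating, the true difference would be known and the whole discrepancy would come from the rule. The document gives no split. Deviators may also come on top of the 20%.

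**5. Direction.** Two further assumed cases, removing non-responders only:
- 16/20 v 10/20 (30 points), 4 removed from the worse arm: 16/20 v 10/16 = 80.0% − 62.5% = 17.5 points. The difference shrinks.
- 14/20 v 10/20 (20 points), 4 removed from each arm: 14/16 v 10/16 = 87.5% − 62.5% = 25 points. The difference grows.

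**The case against.** The contradiction is hard to contest: the article states both rules, so nothing here is left to a fuller document. The objections bear on what one may build on it, and most of them stand.

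- A reader might infer that the rule deletes treatment failures. The document does not establish that. A request to stop need not be a failure, and a new disease may have nothing to do with dentin hypersensitivity. Exclusion can depend on outcome; it need not.
- A reader might infer that the estimate is biased upward, or that the arm failing more often is favoured overall. An arm's response rate rises if its non-responders are the ones removed, but the difference between arms can move either way, as step 5 of the working shows.
- The 20% is a dropout allowance, not a forecast of exclusions under this rule. Treatment is one application at one visit, so many losses may be missed week-4 visits.
- The missing-data clause follows a sentence about the primary outcome and may refer only to that. Loss of a complete VRS through a missing GI or PI is therefore possible, not certain.
- It is tempting to say that the unblinded operator can steer exclusions. The operator keeps the intervention record, but no section says who decides exclusions. Participants are blinded, and the examiner who enrols and assesses them is described as blinded to allocation.
- This is a pilot, which lowers the inferential stakes. It does not remove the problem, because the estimates are meant to inform a later trial's size.

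**Conclusion.** Wrong as written. The Statistical design section names one analysis population and then prescribes another, and the ban on additional analyses leaves no planned check of the difference. As it stands, the primary analysis is per-protocol and complete-case.

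The document does not allow the size or direction of any bias to be stated. The 10 to 50 point range shows only that exclusions on the scale of the plan's own dropout allowance could decide the result. It rests on an assumed binary response, assumed counts and balanced exclusions, and part of it would remain under a correct ITT analysis.

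**What to change.** Replace the exclusion sentence and the sentence that follows it so that the section states:

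1. Every randomised participant with an observed week-4 VRS is analysed in the allocated arm, regardless of discontinuation, deviation, or a missing GI or PI.
2. A missing week-4 VRS is handled by one simple stated rule, for example counted as no improvement, with best/worst-case bounds as a sensitivity analysis.
3. The present exclusion rule is kept only as a labelled per-protocol analysis.
4. The ban on additional analyses is removed, since items 2 and 3 need it gone.

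Multiple imputation is not needed. There is no standard way to pool Fisher's exact p-values across imputations, and with about 20 per arm a single rule with bounds is easier to defend.

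The Blinding of participants section allows allocation to be disclosed on events that largely match the reasons for discontinuing. Any VRS collected after disclosure should be kept and flagged.

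If the sponsor prefers the present exclusions, the minimum correction is to drop the ITT label and call the set per-protocol. The cost is protocol wording and a few extra tabulations, with no visit beyond the planned week 4. Since the article reports recruitment as under way, the change should be made as a dated amendment before the outcome data are analysed.

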### Randomized allocation

After enrollment, baseline assessments will be performed by the examiner who enrolled the participant in this study. Randomized allocation will then be performed in a 1:1 ratio by the dentist in charge of the patient with opaque, sealed envelopes prepared before participant recruitment and on which “Nanoseal” or “CAREDYNE Shield” is printed. Participants allocated to the intervention group will be treated with CAREDYNE Shield, while those allocated to the control group will be treated with Nanoseal. The information on the desensitizers used in this study is described in Table 4.

**Table 4 Tab4:** Desensitizers used in this study

**Material**	**Manufacturer**	**Composition**
CAREDYNE Shield	GC Dental Industrial Corporation, Tokyo, Japan	Solution A: fluorozinccalciumsilicate glass Solution B: 10–15% phosphoric acid
Nanoseal	Nippon Shika Yakuhin Co., Ltd., Shimonoseki, Japan	Solution A: fluoroaluminocalciumsilicate glass Solution B: 10% phosphoric acid

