### Monitoring

Monitoring will be performed by one of our research staff according to the standard operating procedures and the results will be given to the principal investigator within 2 weeks after monitoring. When adverse events or other unintended effects of the intervention happen, the principal investigator will perform appropriate treatments for the participant, report the incident to the Nagasaki University Hospital Clinical Research Ethics Committee (REC) and share this information with the research staff. A data monitoring committee is not necessary because DH treatment with Nanoseal or CAREDYNE Shield is general practice and a low-invasive intervention procedure.

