### Potential benefits and harms

This study will contribute to future clinical improvements. However, atopic dermatitis is a potential side effect of the intervention.

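### Read literally, the analysis rules leave GI and PI unanalysed and drop participants who discontinue for worsening, and no by-arm summary of harms is planned

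*Protocol article*

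**What the plan says.** All references are to the protocol article.

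- **Statistical design.** The primary outcome is tested with Fisher's exact test under an intention-to-treat label. Participants who discontinue, deviate or have missing data are left out. The section closes with "No additional analyses will be performed".
- **Secondary outcome.** Change in GI near the treated area and in PI at the treated surface, from baseline to 4 weeks, scored by inspection and palpation.
- **Discussion.** A fall in GI or PI would prompt a future study. Nothing is said about a rise. The agents are described as acting on tooth structure alone, and "they can, therefore, be casually applied to subgingival areas and proximal surfaces".
- **Intervention.** Worsening or newly arising disease is one of the listed reasons for discontinuing.
- **Participant timeline, Table 2.** One visit after allocation, at 4 weeks (range 3 to 5), with air blow, inspection and palpation.
- **Data collection.** The form holds the examiner, the date, the type of teeth and the outcomes.
- **Monitoring.** The rule starts from the event: "When adverse events or other unintended effects of the intervention happen", the principal investigator treats the participant, reports to the ethics committee and informs staff.
- **Potential benefits and harms.** One harm is named: "However, atopic dermatitis is a potential side effect of the intervention".
- **Sample size.** "at least 15 participants will be required in each group to perform a sample size calculation in a subsequent study", and "With a 20% dropout rate, a total of 40 participants will be recruited in this study".

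**The concern.** Three stated rules combine badly. A secondary outcome is defined and given a purpose, but the analysis section names no analysis for it and rules out any other. A participant whose condition worsens may be discontinued, and a discontinued participant is excluded, so poor tolerability is filtered out of the analysed data by rule. The one harm that the article names is a skin reaction, and no scheduled item would pick it up.

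The pilot exists to inform a larger trial. Its team could reach that planning stage with a comparison restricted to participants who did well enough to stay in, and with no agreed account of what went wrong in each arm.

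**Working it through.** **1. The passages side by side**

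| Topic | One place | Another place | Result |
|---|---|---|---|
| GI and PI | Secondary outcome: change over 4 weeks; Discussion: a fall will be acted on | Statistical design: primary outcome only, nothing further | Outcome defined and relied on, but literally unanalysed |
| Worsening | Intervention: a reason to discontinue | Statistical design: those who discontinue are excluded, under an intention-to-treat label | Poorly tolerating participants leave the analysed set |
| Named harm | Potential benefits and harms: a skin condition | Table 2 and Data collection: no skin or adverse-event item | Recorded only if it comes to light |
| Tissue effects | Potential benefits and harms: a skin side effect is possible | Discussion: agents act on tooth structure alone | Wording needs reconciling |

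**2. The plan's own figure**

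Inputs from Sample size: 15 per group, 20% dropout, 40 in total. Input from Randomized allocation: 1:1.

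15 / (1 − 0.20) = 18.75, rounded up to 19 per group, or 38 in total. The stated 40 (20 per group) agrees with this after rounding up. Expected completers are 20 × 0.80 = 16 per group. Sample size is not at issue here.

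**3. What the exclusion can do (illustration, counts assumed)**

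Suppose 2 of 20 in one arm are discontinued for worsening. Over everyone treated the rate is 2/20 = 10%. In the analysed set it is 0/18 = 0%.

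**4. What a by-arm harm count could show**

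The article gives no expected event rate, so a range of true risks p is assumed.

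Chance of at least one event in n participants = 1 − (1 − p)^n:

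| p (assumed) | n = 15 | n = 16 | n = 20 |
|---|---|---|---|
| 1% | 14.0% | 14.9% | 18.2% |
| 5% | 53.7% | 56.0% | 64.2% |
| 10% | 79.4% | 81.5% | 87.8% |

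Upper limit when no event is seen: one-sided 95% = 1 − 0.05^(1/n); two-sided 95% = 1 − 0.025^(1/n).

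| n | One-sided | Two-sided |
|---|---|---|
| 15 | 18.1% | 21.8% |
| 16 | 17.1% | 20.6% |
| 20 | 13.9% | 16.8% |

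Fisher's exact test (two-sided) with 20 per arm gives p = 0.106 for 4 events against 0, and p = 0.047 for 5 against 0. A comparison of harms would therefore detect only gross differences. The case for the table is description, not testing.

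**The case against.** The strongest reply is that this is an article condensing a fuller protocol (version 1.4.0) that is not shown. Adverse-event forms and safety tables commonly sit in such documents, so their absence is not in itself a fault. The closing sentence of Statistical design may also have been meant to exclude subgroup or adjusted analyses. Both points have force. But the exclusion rule and the bar on other analyses are stated, not omitted, and the text does not limit the bar to subgroup or adjusted work.

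A reader might also infer several stronger things that the article does not support:

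- **That no harm check is scheduled.** The GI is scored near the treated area at both visits by an examiner who is blinded to allocation, so persistent gingival worsening would be seen. What is missing is an item for symptoms or reactions between visits.
- **That GI is used only to show benefit.** The outcome is defined as change, which covers both directions. Only the Discussion is one-sided.
- **That tolerability by arm cannot be reported.** Incidents go to the ethics committee, and allocation is kept in the medical record, so counts by arm remain possible. They are simply not planned.
- **That the test product is singled out by its acid.** Table 4 lists phosphoric acid for both products. The test product reads "Solution A: fluorozinccalciumsilicate glass Solution B: 10–15% phosphoric acid" against 10% for the control, so only the upper end of the range differs.
- **That the general-practice description under Monitoring contradicts Sample size.** The statement "No previous clinical studies have investigated the effectiveness of CAREDYNE Shield on DH" concerns effectiveness and is silent on safety experience. Both can be true.

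Exclusion from the primary analysis also does not cancel the duty to report an incident. It removes that participant's outcome data, not the incident report.

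**Conclusion.** The point holds in a limited form. Followed as written, Statistical design leaves GI and PI unanalysed and excludes participants who discontinue for worsening. No by-arm account of harms is planned, and a transient early reaction can be missed because nothing scheduled asks about it.

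The consequence is modest. At assumed risks of 1%, 5% and 10%, the chance that 20 treated participants include at least one affected is 18%, 64% and 88%. How many of these would go unrecorded cannot be derived from the article. Even complete recording would support only description: no events in 20 is compatible with a risk of up to 13.9%, and in 15 with up to 18.1% (one-sided 95%).

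The conclusion rests on a literal reading of the closing sentence of Statistical design. If the full protocol already limits that sentence and provides for adverse-event recording and a by-arm summary, what remains is to bring the article's wording into line and to settle the exclusion rule. The change is worth making because it is cheap. The finding does not invalidate the trial.

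**What to change.** 1. **Statistical design.** Replace "No additional analyses will be performed" with a statement to this effect: *Changes in GI and PI, in both directions, and adverse events will be summarised descriptively by allocated arm for everyone treated, including those who discontinue. No further subgroup or adjusted analyses are planned.* GI and PI for participants who discontinue would be included where measured.
2. **Table 2 and Data collection.** Add one open question at the existing week-4 visit, asked by the blinded examiner, on any reaction since treatment, with onset and resolution. Add the matching field to the assessment form.
3. **Potential benefits and harms, and Discussion.** Reconcile the two statements on tissue effects. Which of them should change is for the investigators to decide.

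**Cost.** One question and one descriptive table, with no new visit, no new test and the total still 40. Open questioning will record some unrelated minor complaints. Because recruitment is described as under way, the question can apply only to visits still to come, and the report should say how many participants were asked.

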## Abstract

**Background:**

Dentin hypersensitivity (DH) is a condition characterized by short and sharp episodes of pain which will arise in response to tactile, chemical, thermal, evaporative or osmotic stimuli. The painful symptoms cause discomfort in patients and reduce their quality of life. Recently, the novel zinc-containing desensitizer CAREDYNE Shield has been developed as a new type of desensitizer that acts by inducing chemical occlusion of dentinal tubules, and releasing zinc ion for root caries prevention. However, the clinical effectiveness of CAREDYNE Shield on DH remains unclear. Therefore, the aim of this study is to evaluate the effectiveness of CAREDYNE Shield on DH by comparing with that of another desensitizer, Nanoseal, commonly used in Japan.

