Recently, the fluorozinccalsiumsilicate-based desensitizer CAREDYNE Shield (GC Dental Industrial Corporation, Tokyo, Japan) has been developed. It acts as a desensitizer by inducing chemical occlusion of dentinal tubules and contains a novel functional filler that releases not only ions, such as calcium and fluorine, but also zinc. Zinc has been reported to reduce the demineralization of enamel and dentin, and inhibit dentin collagen degradation, plaque growth and biofilm formation [11, 12].

However, the effectiveness of CAREDYNE Shield on DH still remains unclear; therefore, the aim of this study is to investigate the effectiveness of CAREDYNE Shield on DH by comparing with that of Nanoseal. The PICO question of this study is described in Table 1.

**Table 1 Tab1:** PICO question

**Criteria**	**Description**
P (participants)	Non-carious human permanent teeth with DH
I (Intervention)	DH treatment with CAREDYNE Shield
C (Control)	DH treatment with Nanoseal
O (Outcome)	The reduction of pain level in response to air stimuli

*DH* dentin hypersensitivity

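### The pilot is meant to size a later trial, but its analysis section plans one significance test and rules out the estimates that sizing needs

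*Protocol article*

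**What the plan says.** The protocol article gives the pilot's purpose in two places. The Sample size section says that "at least 15 participants will be required in each group to perform a sample size calculation in a subsequent study", and then "With a 20% dropout rate, a total of 40 participants will be recruited in this study". The Discussion says that "this study is being performed for sample size calculations, which is based on the primary outcome", and uses this to justify assessing air stimuli only. It adds that a fall in GI or PI, if seen, would lead to a further clinical study.

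The aim is worded differently. In the abstract, "the aim of this study is to evaluate the effectiveness of CAREDYNE Shield on DH" is the objective, and in the Background section "the aim of this study is to investigate the effectiveness of CAREDYNE Shield on DH by comparing with that of Nanoseal".

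The Statistical design section names one analysis, Fisher's exact test on the primary outcome, and ends with "No additional analyses will be performed". The primary outcome is the reduction on a 0-4 VRS from baseline to 4 weeks. The article does not say how this reduction is grouped into categories for the test.

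**The concern.** A later trial is sized from a plausible difference together with either a spread (for a mean change) or response proportions (for a binary endpoint). The analysis section commits to none of these as an output and excludes anything beyond the test. The GI and PI changes, on which the Discussion relies, are not analysed at all.

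The aim adds to the problem. It speaks of effectiveness against an active comparator, while the only planned result is a p-value from at most 40 people. A non-significant result would show neither that CAREDYNE Shield works better nor that it works about as well as Nanoseal. Followed literally, the plan would leave the designers of the next trial without the figures that this trial was set up to provide.

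**Working it through.** **Step 1: the plan's own figure.** Inputs from the Sample size section are 15 per group and 20% dropout. The Randomized allocation section gives the ratio: "Randomized allocation will then be performed in a 1:1 ratio".

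15 / (1 - 0.20) = 18.75, so 19 per arm and 38 in total. The stated 40 (20 per arm) is this figure rounded up, so it reproduces. With 20% loss, 40 × 0.80 = 32 remain, or 16 per arm. The cases to examine are therefore 15 (the stated minimum), 16 (after the expected loss) and 20 (no loss) evaluable per arm.

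**Step 2: what is needed against what is planned.**

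| Needed for the stated purpose | In the Statistical design section |
|---|---|
| Spread or distribution of VRS reduction per arm | Not planned |
| Between-arm difference with confidence interval | Not planned |
| Response proportions, if the endpoint is binary | Not named as an output; no categories given |
| GI and PI change | Not planned |
| Test of the primary outcome | Fisher's exact test |
| Anything else | Excluded |

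**Step 3: what the test can show if the endpoint is binary.** The article gives no significance level and no response rates. I assume a two-sided 0.05 level, two response categories and the rates below. Power is the sum, over all pairs of counts (x, y) with Fisher p ≤ 0.05, of Bin(x; n, p1) × Bin(y; n, p2).

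| Assumed rates | 15 per arm | 16 per arm | 20 per arm |
|---|---|---|---|
| 50% vs 70% | 10% | 12% | 16% |
| 50% vs 80% | 25% | 28% | 41% |
| 50% vs 90% | 54% | 58% | 74% |
| 50% vs 50% (type I error) | 1.7% | 2.0% | 2.0% |

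The 95% half-width for a difference in proportions near 50% is 1.96 × √(2 × 0.5 × 0.5 / n). This gives 0.358, 0.346 and 0.310, or about 36, 35 and 31 points.

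**Step 4: a separate illustration, if the later trial compares mean VRS reduction.** This treats the change as roughly normal, which is an approximation for a 0-4 score. It is an alternative to step 3, because the two do not describe the same endpoint.

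- The 95% limits for a pooled SD are √(df / χ²) times its estimate, with df = 2n - 2. At 16 per arm (df = 30) the factors are 0.80 and 1.34. The later sample size is proportional to SD², so it is known only to within 0.64 to 1.79 times.
- The half-width for the mean difference, t × √(2/n), is 0.75, 0.72 and 0.64 SD at 15, 16 and 20 per arm.
- For an assumed 0.5-point difference at 80% power, n per arm = 2 × (1.96 + 0.84)² × SD² / 0.5². This gives 31, 51, 76 and 107 for assumed SDs of 0.7, 0.9, 1.1 and 1.3.

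The next trial's size therefore depends heavily on a spread that this plan does not undertake to report.

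**The case against.** The strongest reply is that the closing sentence means only that there will be no subgroup or adjusted comparisons. The Discussion supports this: it expects to observe GI and PI changes and to base a calculation on the primary outcome, so the authors presumably intend to summarise the data. The article also condenses a fuller protocol, and descriptive estimates are often left to that document or to an analysis plan. Their absence alone would be no fault. What remains is that the sentence is unqualified. Read literally, it contradicts the Discussion, and a fuller document that added estimation would conflict with it.

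A reader might infer more than the article supports:

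- **That nothing usable for planning could come out.** The counts in a Fisher table would give response proportions, which are enough to size a binary endpoint. The VRS scores are collected and would yield an SD. The fault lies in what is planned and excluded, not in the data.
- **That the dropout rate would be lost.** The article commits to CONSORT and a flow chart, which would ordinarily show losses.
- **That an equivalence claim is planned.** Nothing in the article says so, and it calls the trial a pilot. Misreading a non-significant result is a risk to guard against, not a stated intention.
- **That a non-significant result is assured.** The power figures rest on assumed rates and reach 58-74% for 50% vs 90% with 16 to 20 per arm.
- **That 40 patients are too few.** The number follows from a rule of thumb for pilots and is not challenged here.

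**Conclusion.** The point holds as an internal conflict. The pilot's declared purpose calls for estimates, while its analysis section plans a single test and, in unqualified words, excludes the rest. The same wording leaves GI and PI unsummarised although later work depends on them. The mismatch between an effectiveness aim and a pilot purpose is secondary but should be corrected at the same time.

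The conflict itself rests on the article's text alone. The figures for its size are illustrations that depend on the assumed level, response rates, difference and SDs. The data remain recoverable and the repair is wording plus simple summaries, so this is a point that should be fixed and not one that undermines the trial.

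**What to change.** Replace the last sentence of the Statistical design section with a statement along these lines:

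- The main analysis is estimation: the distribution and SD of VRS reduction in each arm, and the between-arm difference with a 95% confidence interval.
- If a responder endpoint is intended, its categories are defined and the proportion in each arm is reported.
- GI and PI changes are summarised descriptively by arm.
- Fisher's exact test is exploratory, and no conclusion of effectiveness or similarity rests on its p-value.

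Reword the aim in the abstract and the Background section to match the pilot purpose. If the closing sentence was meant to exclude only subgroup or adjusted analyses, it should say so.

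The cost is a protocol wording change, a few summaries of data already being collected, and a more modest stated aim. No patients or visits are added. How conservatively to use the SD when sizing the next trial can be left to that trial.
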